### Potential limitation and bias

2.9

#### Selection bias

2.9.1

It is defined as the representation of the results of a sample that is not representative of the entire population concerned. Our study might be subject to this bias since only voluntary, and therefore motivated patients will be included in our study. Documenting the reasons for non-participation is a planned strategy to limit this bias.

#### Attrition bias

2.9.2

The attrition bias is defined as the observation of systematic differences between groups due to premature withdrawal from the study leading to incomplete results data. To reduce the effect of this bias, the “intention to treat” analysis will be adopted, which means that the analysis will take into account all included patients who have completed the study or not.

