### Design

2.1

This study aims to evaluate the feasibility, acceptability and pre-test the impact of a nursing consultation and tele-monitoring in Lebanon. It will be conducted at the Hôtel-Dieu de France (HDF) hospital, one of the largest university hospitals in Beirut, and will use quantitative and qualitative methods in pre- and post-intervention to collect data over a period of 3 months with a single group intervention. Data will be collected by 2 researchers. A consent form will be signed by each participant before the intervention. Patients will be informed about the purpose of the study, the course of the intervention, and the freedom to withdraw from the study at any time. Their consent for the video recording will also be taken.

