#### Third phase

2.6.3

During this last session that takes place at the nurse's office, quality of life of participants, their respiratory health status, and their level of anxiety will be reevaluated. A second educational diagnosis will be performed and compared to the first one. At the end of the session, patients will be asked to complete sheet 2 of the evaluation that includes 4 parts about their perception of the acceptability, adequacy, adoption, and cost of the program.

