### Sample size calculation

2.7

Since this is a feasibility study with an intervention that has never been tested before on the Lebanese population, no formal calculation of the sample size will be performed, and 30 patients with moderate to severe COPD will be recruited, based on Hertzog's recommendations: a sample of 10 to 40 people is sufficient for a pilot study using a single group to estimate sample size for a future trial.^[35]^

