### Analyses

2.8

To determine the feasibility of this research program, 6 variables will be selected: acceptability, adoption, adequacy, fidelity, cost and coverage, with 2 types of participants: COPD patients and researchers. Patients will assess acceptability, adoption, adequacy and cost, while researchers will assess the fidelity, cost and coverage of the program.

Analyses will be performed on SPSS version 25 (IBM SPSS Statistics for Windows). Student *t* test will be used to compare normally distributed continuous variables between 2 groups, ANOVA test between 3 groups or more, and Chi-square for binary and/or categorical variables. Open ended questions will be analyzed narratively.

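### Section 2.9.2 relies on intention to treat against attrition bias, but as described the immediate pre-post change and the sheet 2 results would rest on final-visit attenders only

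*Protocol article*

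**What the plan says.** Section 2.1 describes a study "with a single group intervention", in which patients are told of "the freedom to withdraw from the study at any time". Section 2.7 states that "30 patients with moderate to severe COPD will be recruited", with no formal calculation and no expected dropout.

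Section 2.9.2 defines attrition bias as "the observation of systematic differences between groups due to premature withdrawal from the study leading to incomplete results data". Its remedy is an intention-to-treat analysis, explained as meaning that "the analysis will take into account all included patients who have completed the study or not".

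The collection points are these:

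- **First consultation (2.6.1):** baseline quality of life, respiratory status and anxiety, plus sheet 1 on acceptability, adequacy, adoption and cost.
- **Six home sessions (2.6.2):** acceptability and cost of each session, and an open question.
- **Final office session (2.6.3):** the same three health measures again. Then: "At the end of the session, patients will be asked to complete sheet 2 of the evaluation".
- **Telephone, one month later (2.6.4):** a third measurement of the three health measures, and hospital and emergency use in that month.
- **Hospital register (2.5):** hospitalisations and emergency visits in the year before and during the programme.

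For analysis, section 2.8 says that the Student *t* "test will be used to compare normally distributed continuous variables between 2 groups", with ANOVA for three or more groups and chi-square for categorical data.

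**The concern.** Intention to treat is a rule about who belongs in an analysis. In a randomised comparison it keeps patients in the arm to which they were allocated. Here there is one group, so neither the between-group definition of the bias nor the remedy fits the design. Taken in the article's own sense, as including completers and non-completers alike, the rule still needs outcome values for the non-completers, and for two sets of results the described collection does not provide them.

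Acceptability is part of the first aim and the effect on quality of life is part of the second; both feed the recommendations for a randomised trial. Patients who leave may include those who found the programme unacceptable or unhelpful. If their end-of-programme answers are absent while the report states that all included patients were analysed, readers may believe that attrition has been dealt with when it has not.

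**Working it through.** **Step 1. What a patient who leaves contributes.** Take a patient who stops after home session 3.

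| Result | Source | Available for this patient? |
|---|---|---|
| Acceptability, early | Sheet 1 (2.6.1) | Yes |
| Acceptability, by session | Sessions 1 to 3 (2.6.2) | Yes, three ratings |
| Acceptability, adequacy, adoption, cost at end of programme | Sheet 2 (2.6.3) | No |
| Immediate post-programme CAT, CCQ, HAD | Final office session (2.6.3) | No |
| One-month quality of life, respiratory status, anxiety | Telephone (2.6.4) | Possible; the text does not say that withdrawn patients are called |
| Hospital and emergency use, prior year and during programme | Register (2.5) | Yes, without a visit |

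The gap is therefore confined to the third and fourth rows. For those rows a *t* test or ANOVA has no post-programme value to use, so the analysed post-programme data are those of final-visit attenders.

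**Step 2. Inputs for size.** N = 30 comes from section 2.7. It rests on a cited rule ("a sample of 10 to 40 people is sufficient for a pilot study using a single group"), so there is no calculation to reproduce; 30 lies inside 10 to 40. The rest is assumed, because the article gives no figures: dropout d of 10% to 40%, about 90% of completers satisfied, and a completer improvement of 0.5 SD.

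**Step 3. Formulas.**

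- Completers n = 30(1 − d); missing m = 30 − n.
- With a satisfied completers (0.9n, rounded), the share over all 30 lies between a/30 (no dropout satisfied) and (a + m)/30 (every dropout satisfied).
- If dropouts do not change, the all-patient mean change is 0.5 × n/30 SD, so the completer mean overstates it by 0.5 × m/30 SD.
- The half-width of a 95% interval for mean change is t(0.975, n − 1)/√n, in SDs of change.

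**Step 4. Results.**

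| Dropout | n | m | Satisfied completers | Range over all 30 | Overstatement of change | Half-width |
|---|---|---|---|---|---|---|
| 0% | 30 | 0 | 27/30 = 90% | 90% | 0 | 0.37 SD |
| 10% | 27 | 3 | 24/27 = 89% | 24/30 to 27/30 = 80–90% | 0.05 SD | 0.40 SD |
| 20% | 24 | 6 | 22/24 = 92% | 22/30 to 28/30 = 73–93% | 0.10 SD | 0.42 SD |
| 30% | 21 | 9 | 19/21 = 90% | 19/30 to 28/30 = 63–93% | 0.15 SD | 0.46 SD |
| 40% | 18 | 12 | 16/18 = 89% | 16/30 to 28/30 = 53–93% | 0.20 SD | 0.50 SD |

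The completer proportion stays near 90% in every row, while the lower end of what is compatible with all 30 patients falls steadily.

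**The case against.** The strongest reply has four parts.

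1. **Much of the data does not depend on the final visit.** This is correct and it limits the point. Step 1 shows that a patient leaving after session 3 has already given four acceptability ratings (sheet 1 and three sessions). Register data need no attendance, and the telephone evaluation needs no office visit. It is tempting to infer that all post-programme data, or all acceptability data, come from completers; the article does not support that. The call does not close the gap, however. It is timed from the last intervention, nothing says that patients who withdrew will be called, and sheet 2 is not among the items listed for it.

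2. **Missing-data handling may sit in an analysis plan that is not shown.** This also stands, and it is why the conclusion is worded as what would follow from the procedures described. But section 2.9.2 asserts that a named approach reduces attrition bias, and that assertion can be judged as it stands. An analysis plan would not alter the between-group definition, and it could not recover sheet 2 answers that were never sought.

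3. **The label is explained in the same sentence and is workable in one arm.** As a statement of who is included, yes. As a remedy for absent outcomes, no.

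4. **Dropouts may leave for illness or other reasons unrelated to the programme.** This is fair. The lower bounds in the table treat every dropout as dissatisfied and are worst cases.

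**Conclusion.** The point holds in a limited form. The protection claimed in section 2.9.2 is not delivered by the collection and tests described, for two sets of results: the immediate pre-post change in CAT, CCQ and HAD, and the end-of-programme sheet 2. As described, these would be completer results and may be too favourable.

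The size cannot be known, since neither a dropout rate nor reasons for leaving are given. Under the stated assumptions, acceptability over all 30 could lie between 80% and 90% at 10% dropout and between 63% and 93% at 30%. The mean change would be overstated by 0.05 SD at 10% dropout and 0.20 SD at 40%, if completers gain 0.5 SD and dropouts nothing.

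A reader might infer that the study will report about 90% acceptability whatever the dropout. That would require sheet 2 to be the only source and completers to be the denominator; the article states neither, and acceptability is also rated at the first consultation and at every home session. This is worth correcting, but it does not undermine the study as a whole.

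**What to change.** In section 2.9.2:

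1. Describe attrition bias for a single group, as a difference between patients who remain and those who leave, and replace the intention-to-treat wording with 'all enrolled patients'.
2. State that, unless consent is withdrawn, patients who stop will be asked by telephone for sheet 2 and for CAT, CCQ and HAD, and will be included in the one-month call.
3. Report acceptability and adoption over all 30, with the number having data at each time point, and use the session ratings already given by those who leave.
4. Add two sensitivity analyses: one counting dropouts (or those leaving for programme-related reasons) as not accepting, and one assuming no change from baseline in CAT, CCQ and HAD for those without post-programme values.

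The register reading is already planned and needs no change. The cost is some wording and a few extra calls, using telephone contact and session ratings that the study already has. The downside is that the acceptability figures may look less favourable.

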#### Social desirability bias (Hawthorne effect)

2.9.3

It is defined by the observed positive effect that is not related to the intervention but simply due to the fact that this group feels observed, hence the modification of its behavior. This limitation can be observed in our study since the protocol design does not include a blind group. A telephone follow-up is therefore considered 1 month after the intervention to evaluate the maintenance of the acquired skills.

#### Confirmation bias

2.9.4

This tendency to favor information that confirms preconceived ideas can be observed in our study in the need to judge whether the intervention was actually received and faithful to the original protocol. To reduce the effect of this bias, a second judge will be asked to evaluate this step.

## Discussion

3

As the prevalence of COPD continues to increase, so does its cost to the healthcare system. Self-management has been shown to be an effective component of chronic care, yet the impact of tele-monitoring has not been yet established as a support for a self-management program. This proposed intervention may improve the quality of life and reduce emergency visits and re-hospitalization rates of Lebanese patients with COPD; it may also be extended to COPD patients in any developing country with no specific educational program for this population.

Results of this innovative study in Lebanon will establish feasibility and provide preliminary evidence on the efficacy of this intervention, and could potentially influence clinical practice and health policy in Lebanon.

### Trial status

3.1

This protocol is registered on clinicalTrials.gov 11 December 2019, NCT04196699.

At the time of manuscript submission, participant will be recruited.
